##### Couple-Level Dependence

Because participants are recruited and randomized as couples, observations within a dyad are nonindependent. This clustering is addressed through the inclusion of couple-level random effects in all mixed-effects models. As a sensitivity analysis, generalized estimating equations with an exchangeable working correlation structure (*geepack*) will also be estimated to obtain population-average intervention effects.

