This study is designed as a randomized, parallel-group, superiority trial with 3 arms and a 1:1:1 allocation ratio. An a priori power analysis was conducted to determine the necessary sample size to detect a meaningful effect in the primary outcome measure. Considering the study design, an estimated effect size of *d*=0.4, statistical power of 0.9, and α level of .05, the required sample size was calculated to be 84 heterosexual couples. To account for potential attrition (estimated at 7%), a total of 90 couples will be recruited. While the a priori power calculation was based on a standard framework, the final sample (N=180 individuals; 90 units of randomization and 30 couples per experimental condition) was increased to provide additional robustness for the planned longitudinal and dyadic analyses. The sample size estimation was based on a conservative effect size derived from prior studies. Although the calculation does not explicitly model the multilevel structure of the data (ie, repeated measures nested within individuals and couples), the use of mixed-effects models in the analysis phase is expected to appropriately account for this dependency structure. The allocation sequence will be computer-generated using random block sizes of 3 or 6 by a research assistant not involved in recruitment, assessment, or intervention delivery. Allocation will be concealed until participant enrollment and completion of baseline assessments (see Figure 1).

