#### Quantitative Analysis

##### Primary Analysis

The primary outcome is the change in beliefs related to sexual aggression. The primary comparison of interest is the condition × time interaction—specifically, whether change from baseline to postintervention and from baseline to 3-month follow-up differs across the 3 experimental conditions (IVR-based intervention, control condition A, and control condition B). This will be estimated using a single prespecified linear mixed-effects model with fixed effects for condition (3 levels, dummy-coded), time (3 levels, with baseline as reference), and their interaction, and random intercepts for couples and for participants nested within couples. The female partner’s scores (eg, Dyadic Adjustment Scale and Couple Flourishing Measure) will be included as covariates to control for baseline relationship quality. This model structure was selected as the primary analytic approach; ANOVA-based omnibus tests and simpler regression models will not serve as primary analyses but may be reported descriptively.

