##### Secondary Outcomes

Empathy, gender attitudes, relationship functioning, and physiological responses will each be analyzed using prespecified mixed-effects models with the same fixed-effects structure as the primary model, adapted to the distribution of each outcome (eg, binomial models for binary outcomes and Poisson or negative binomial for count outcomes). Eye-tracking and pupillometry measures collected during IVR exposure will be analyzed using linear mixed-effects models with random intercepts for participant and, where applicable, for stimulus item. Descriptive statistics and effect sizes (Cohen *d* or partial *η*²) with 95% CIs will be reported for all outcomes.

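### The couple random intercept drops out of the condition × time contrast, so any linear model fitted to both partners treats their changes as independent

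*Protocol article*

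**What the plan says.** Couple-Level Dependence recognises that partners are not independent, because they are recruited and randomised together, and states: "This clustering is addressed through the inclusion of couple-level random effects in all mixed-effects models". It adds a GEE with exchangeable correlation as a sensitivity analysis and does not name the cluster level.

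Primary Analysis makes condition × time the comparison of interest, meaning differences between arms in change from baseline to postintervention and to 3 months. The random part of that model is "random intercepts for couples and for participants nested within couples". No couple-by-time effect or correlated partner residual is named anywhere.

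Under the data analysis plan, Secondary Outcomes says that empathy, gender attitudes, relationship functioning and physiological responses "will each be analyzed using prespecified mixed-effects models with the same fixed-effects structure as the primary model".

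The Sample section admits that the sample-size calculation leaves out the multilevel structure, but says "the use of mixed-effects models in the analysis phase is expected to appropriately account for this dependency structure". It gives 180 individuals, 90 randomised units and 30 couples per arm.

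**The concern.** A couple intercept captures stable similarity between partners: some couples score higher than others at every visit. The tested effect is about change, and a stable couple effect contributes nothing to change. The dependence that matters is whether partners' scores move together, and the specified model has no term for that.

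There is reason to expect some correlated change. Intervention Procedure has the partners meet in a virtual conversation whose topic differs by condition. On the Dyadic Adjustment Scale (DAS), the Communication Patterns Questionnaire (CPQ) and the Couple Flourishing Measure (CFM), both partners rate the same relationship. Intervention Description relies on dyadic data to judge whether the intervention affects how the couple interact. If those scores are modelled for both partners, the intervals for that question could be too narrow while the article presents the clustering as dealt with.

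**Working it through.** **The plan's own figure.** The article states no error rate for the mixed model. Its one checkable figure is the sample size: "an estimated effect size of *d*=0.4", "statistical power of 0.9, and α level of .05", and "the required sample size was calculated to be 84 heterosexual couples". A repeated-measures group × time calculation with f = d/2 = 0.2, 3 groups, 2 measurements and a between-visit correlation of 0.5 gives N = 84 exactly. The last two inputs are assumptions. That calculation counts each couple once, so it does not settle how two partners per couple are handled later.

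**Inputs.** From the article: 3 arms, 30 couples per arm, 3 visits, intercepts for couple and participant. Two-sided 5% is assumed, since the sidedness is not stated. The within-couple correlation of change, rho, is not given and is varied.

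**Algebra.** For couple c, partner p, visit t:

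y = fixed effects + u(c) + v(p in c) + e(c,p,t)

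Post minus baseline = change in fixed effects + e(post) − e(baseline). Both u and v are gone, and the model takes e as independent between partners.

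Let s² be the variance of one person's change.
- Model's variance of a couple's mean change: s²/2.
- True variance: s²(1+rho)/2.
- Standard error understated by the factor 1/sqrt(1+rho).
- Error df in the stated model: 2 × (180 − 3) = 354. Based on couples: 2 × (90 − 3) = 174.

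**Actual false-positive rate at nominal 5%** (large-sample)
- Single contrast: 2 × (1 − Φ(1.96/sqrt(1+rho))).
- Joint 4-df test: P(χ² on 4 df > 9.488/(1+rho)).

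| rho | single contrast | 4-df test |
|---|---|---|
| 0 | 5.0% | 5.0% |
| 0.05 | 5.6% | 6.0% |
| 0.2 | 7.4% | 9.5% |
| 0.3 | 8.6% | 12.1% |
| 0.5 | 11.0% | 17.6% |
| −0.2 | 2.8% | 1.8% |

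**Simulation** (30 couples per arm, 2 partners, 3 visits, no effect, 20,000 trials per rho). The stated model gave 7.4%, 8.7% and 10.9% for a single contrast at rho 0.2, 0.3 and 0.5, and 9.4%, 12.3% and 17.8% for the 4-df test. Over rho from 0 to 1, single-contrast rates for the alternatives were:
- couple-mean changes: 4.8% to 5.3%
- GEE clustered on couple: about 5.8% to 6.2%
- men only: 4.7% to 5.3%

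**Direct model fit** (one simulated dataset, rho 0.5). The interaction standard error was 0.2646 with intercepts only, equal to sqrt(4 × residual variance/60), so neither intercept variance enters it. Adding a couple-by-time variance gave 0.3234. The ratio 0.3234/0.2646 = 1.22 matches sqrt(1.5) = 1.22.

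**The case against.** The strongest reply concerns scope. Objectives sets the primary outcome, the Acceptance of Modern Myths About Sexual Aggression (AMMSA) scale, in men, and Primary Analysis enters the woman's scores as covariates. Both fit a men-only model, in which this problem does not arise. A reader might infer that the primary test is inflated. The documents do not establish that. They do not exclude it either: with one man per couple the two nested intercepts are the same term and cannot be separated, so the model as written suggests both partners.

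Nor does any section say outright that DAS, CPQ or CFM will be fitted to both partners' rows. Carrying over the primary model's fixed effects would adjust a woman's DAS or CFM for her own score on that scale, which favours men's scores as the outcome. Secondary Outcomes carries over only the fixed effects, and couple-level random effects could in principle include more than an intercept. Against this, the Sample section counts 180 individuals and plans dyadic analyses, and an intercept is the only form specified. So the point stands, but only conditionally.

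Rho may also be small. Partners are in separate rooms, women are in a neutral setting in phase 3 in every arm, and measurement error limits rho (CPQ alpha is 0.62 to 0.84). This is fair, and is why the size is given as a range.

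Finally, the GEE would come close to the nominal level if clustered on couple. It is only a sensitivity analysis with no named cluster level, so it mitigates the problem without removing it.

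**Conclusion.** The statement that couple-level random effects deal with the clustering does not hold for the tested effect in a linear model fitted to both partners with intercepts only. Over rho 0.05 to 0.5, a single change contrast has a false-positive rate of about 5.6% to 11.0% (1.1 to 2.2 times nominal), and the 4-df test about 6.0% to 17.6%.

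Three stronger readings are not supported:
- That false positives triple in general. The 4-df test reaches threefold at rho of about 0.4, but a single contrast needs about 0.8 to 0.9. Primary Analysis describes specific changes from baseline and keeps ANOVA-type omnibus tests out of the primary role.
- That every standard error is too small. This needs rho above 0; with negative rho the test is conservative.
- That a stated 5% is breached for the secondary outcomes. The only alpha in the article belongs to the primary sample-size calculation.

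The result rests on assumed values of rho. Cancellation is exact for linear models with complete data and approximate for binomial or count models.

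**What to change.** In Primary Analysis, Couple-Level Dependence and Secondary Outcomes:
- State which partners enter each model.
- For every model fitted to both partners, add a couple-by-time random effect, for example `(1 | couple) + (1 | couple:time) + (1 | participant)` with unique participant identifiers, or use a dyadic (person × visit) residual covariance. Base the error degrees of freedom for condition × time on couples, about 174 with complete data.
- For DAS, CPQ and CFM, analysing the couple mean at each visit is a simple alternative.
- If AMMSA is analysed in men only, say so and keep one random intercept.
- Amend Couple-Level Dependence to say that the couple intercept alone does not account for correlated change within couples.

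The cost is one variance component and a few sentences, with no new data. Intervals widen by sqrt(1+rho): sqrt(1.05) = 1.02, about 2%, at rho 0.05, and sqrt(1.5) = 1.22, about 22%, at rho 0.5. The extra variance may be estimated at zero where partners' changes are unrelated.

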##### Secondary Outcomes

Empathy, gender attitudes, relationship functioning, and physiological responses will each be analyzed using prespecified mixed-effects models with the same fixed-effects structure as the primary model, adapted to the distribution of each outcome (eg, binomial models for binary outcomes and Poisson or negative binomial for count outcomes). Eye-tracking and pupillometry measures collected during IVR exposure will be analyzed using linear mixed-effects models with random intercepts for participant and, where applicable, for stimulus item. Descriptive statistics and effect sizes (Cohen *d* or partial *η*²) with 95% CIs will be reported for all outcomes.

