### Experimental Design

#### Overview

This study will seek to evaluate the efficacy of REVISE for reducing beliefs related to sexual aggression and influencing related psychological mechanisms, such as empathy and perspective-taking, among heterosexual men. The study includes 3 IVR intervention scenarios (see Figure 1). All conditions will follow the same general format: a 1-hour main session, where participants will be exposed to an IVR setting, followed by a postintervention interview to assess the impact of the experience and follow-up (for details, see Figure 1 and Table 1).

Self-reported questionnaires assessing empathy, gender attitudes, attitudes about sexual aggression, and relationship dynamics will be administered at 3 time points: baseline (preintervention), immediately postintervention, and at a 3-month follow-up. Physiological measures, including eye tracking and pupillometry, will be recorded in real time during IVR exposure to capture participants’ attention and emotional responses. Additionally, questions assessing embodiment will be administered at two key moments during the IVR session: (1) after the mirror embodiment phase and (2) at the end of the experience (farewell phase). Finally, a semistructured interview will be conducted immediately postintervention to explore participants’ subjective experiences, perceptions of the IVR scenario, and reflections on the impact of the intervention on their attitudes and beliefs related to sexual harassment and gender-based violence. The 3 experimental conditions are described in the following subsections.

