### Intervention Procedure

The intervention follows 5 phases, as shown in Figure 1. Each participant will arrive at the laboratory and provide their consent to participate in the study. They will be randomly assigned; participants will be naïve to the study hypotheses. While avatar creation takes place, the couple will answer preintervention questionnaires. Phase 1 also involves the process of personification of the avatar according to the condition in which they will be assigned (see the section on the Intervention Description).

During phase 2, the participants will perform a mirror embodiment task to familiarize themselves with the virtual environment and their new virtual body. More specifically, a female virtual assistant will welcome the participants and instruct them to perform some physical body movements while observing themselves in a virtual mirror. The observation of real-time movements in the embodied avatar, which corresponds to the participants’ real body movements, will allow for greater immersion, as well as enhance body ownership and agency toward the virtual body. For assessment purposes, the female assistant will be a sexualized avatar. During this initial outreach, eye-tracking data will be collected from the participants in relation to the assistant’s cleavage, as gaze fixation on sexualized body parts has been identified as a marker of sexual objectification [47,52]. Once the training and embodiment process is completed, participants will be asked the first questions related to embodiment to check the degree of embodiment achieved.

In phase 3, men will have a 180-second adaptation period in which they will be in an empty bar, and nothing will happen, while women will be in a neutral playful setting in all 3 conditions. Condition 1 men will be involved in a situation of sexual harassment by a group of other men (eg, unwanted flirting, verbal intimidation, and sexist comments). In condition 2, they will stay the same length of time as in the other conditions, but in this case, they will not be sexually harassed. Finally, those in condition 3 will witness the same harassment as in condition 1, but from a bystander perspective, that is, the assaulted person will be a random virtual woman. While people are exposed to the scenarios, their emotional arousal will be assessed by pupillometry in the 3 experimental conditions; however, SAM will be used at the end of phase 3.

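### Physiological outcomes are given the primary model's baseline/post/3-month fixed effects, although they are recorded only within the single IVR session

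*Protocol article*

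**What the plan says.** Under Quantitative Analysis, the Secondary Outcomes paragraph lists empathy, gender attitudes, relationship functioning and physiology together, and states that "physiological responses will each be analyzed using prespecified mixed-effects models with the same fixed-effects structure as the primary model". The Primary Analysis paragraph defines that structure as "fixed effects for condition (3 levels, dummy-coded), time (3 levels, with baseline as reference), and their interaction". It also fixes what time means, since the comparison of interest is "whether change from baseline to postintervention and from baseline to 3-month follow-up differs across the 3 experimental conditions".

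The questionnaires fit this, being "administered at 3 time points: baseline (preintervention), immediately postintervention, and at a 3-month follow-up" (Experimental Design, Overview). The physiological measures do not: the same section says that they "will be recorded in real time during IVR exposure". Table 1 marks them once, on the intervention day, with nothing at 1 week or 3 months. The Intervention Procedure section places gaze recording in phase 2 (mirror task) and phase 5 (farewell), and describes pupillometry during the phase 3 scenario.

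A second sentence in the Secondary Outcomes paragraph deals with eye tracking and pupillometry alone. It names linear mixed models with random intercepts for participant and, where relevant, stimulus item. It does not mention fixed effects or a time factor.

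**The concern.** The time factor in the assigned model is a study visit. The physiological data vary by phase within one visit. Terms for visits at which nothing is recorded cannot be estimated.

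The Objectives section makes change in gaze and pupil response across conditions, during the VR experience, a secondary objective. If the prespecified model cannot deliver that contrast, someone must later choose the phase, the reference window and the people who enter the analysis, possibly with the data in view. The primary AMMSA analysis is not affected.

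**Working it through.** The plan gives no figure on this point to reproduce. The check is which coefficients the stated fixed effects can estimate, given when each measure is taken.

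**Inputs.** There are three conditions and one model with a three-level time factor (Primary Analysis). The recording occasions come from Table 1, the Overview and the Intervention Procedure. The check used 30 men per arm; the result does not depend on that number.

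**Columns in the stated model**, before covariates: 1 intercept + 2 condition + 2 time + (2 × 2) interaction = 9.

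**Rule.** If a measure is observed at T of the time levels in every arm, 3 × T condition-by-time cells hold data, so the rank is 3T. With baseline among the observed levels, (3 − 1) × (T − 1) interaction coefficients are estimable.

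| Measure and reading | T | Rank | Interaction terms estimable |
|---|---|---|---|
| Questionnaires at three visits | 3 | 9 of 9 | 4 of 4 |
| Pupil, phase 3 scenario only | 1 | 3 of 9 | 0 of 4 |
| Gaze, phase 2 read as baseline and phase 5 as post | 2 | 6 of 9 | 2 of 4 |

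Building the design matrices numerically gave the same ranks and counts. For pupil it makes no difference whether the single occasion is labelled baseline or postintervention: the rank is 3 and no interaction term is estimable. For gaze, the two terms left without data are the condition-by-3-month terms.

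**With a within-session factor instead.** For gaze, condition by a two-level phase has 1 + 2 + 1 + 2 = 6 columns and rank 6, so both interaction terms are estimable. For pupil in the scenario alone, an intercept and two condition contrasts (3 parameters) are estimable. A condition-by-window interaction needs a second recorded window.

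**Phase 2 is not a pre-treatment baseline.** Avatars are assigned by condition in phase 1, and the mirror task is done in that avatar. Men in conditions 1 and 2 are therefore already in the partner's body when phase 2 gaze is measured. A phase 2 to phase 5 change removes any effect that embodiment has already had by phase 2, so the interaction alone does not carry the whole arm comparison.

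**The case against.** The strongest reply is that the second sentence is the specific rule and displaces the general one. It refers to data collected during exposure, and an intercept for stimulus item suits within-session records rather than visits. The objective is also framed within the session. On that reading only an unnamed phase factor is missing, which an article may leave to the full plan.

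Part of this stands: the authors may well have intended a within-session model. But the first sentence names physiological responses explicitly and assigns them a definite structure, and the second puts no other in its place. If it supplements the first, the unusable terms remain. If it replaces the first, the article contradicts itself about the fixed effects and states none. Either way the text is wrong as it stands, not merely brief.

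Three stronger readings are tempting but not supported:

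- **That nothing can be estimated for gaze.** Gaze has one occasion before the scenario and one after it, and baseline, session and posttest share the intervention day. Two of the four terms survive on the generous mapping.
- **That partners would be treated as independent.** The second sentence does not mention a couple intercept, but the Couple-Level Dependence paragraph promises "inclusion of couple-level random effects in all mixed-effects models", and nothing exempts physiology.
- **That pooling the sexes would halve the effect.** In phase 3 the men meet the scenario "while women will be in a neutral playful setting in all 3 conditions", so one might infer that an effect d in men becomes d/2. No section says that women's recordings will be pooled without a sex term, and the objectives and hypotheses concern men. Women's gaze in phases 2 and 5 could itself differ by arm, because identity exchange and the phase 4 discussion do.

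**Conclusion.** The point holds in a bounded form. The fixed effects assigned to physiological responses do not match when those responses are recorded. Both condition-by-3-month terms are empty for every physiological measure. No condition-by-time term is estimable for pupillometry, and at most two of four are for gaze.

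This assumes that Table 1 and the Overview are complete, so that there is no recording outside the session, and that pupil data are used only from the phase 3 scenario, as described. If pupil recording also covers the 180-second adaptation period, a within-session contrast is possible, but it is still not the one stated. This is a definite error in the model for a secondary objective. It should be corrected, but it does not threaten the primary result.

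**What to change.** In the Secondary Outcomes paragraph, take physiological responses out of the sentence that assigns the primary model's fixed effects, and state a separate model for men, the target of the objectives:

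- **Gaze:** condition, phase (2 v 5) and their interaction, with arm contrasts also reported within each phase, because avatar assignment precedes phase 2.
- **Pupil:** arm contrasts during the phase 3 scenario. If the sponsor confirms that pupil data are captured in the 180-second adaptation period, use it as the reference and fit condition, window and their interaction.
- **Random effects:** an intercept per man wherever he contributes more than one record. With one man per couple, a couple intercept coincides with the participant intercept and is not needed. The Couple-Level Dependence paragraph should state this exception.

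The cost is analysis wording and one check with the sponsor on the adaptation period. The gaze phases are already scheduled. The Results section reports that recruitment had not begun as of January 2026, so the change can be made before any data are seen.

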## Methods

### Objectives

The primary objective of this randomized controlled trial is to evaluate the efficacy of the REVISE intervention in reducing beliefs that legitimize or minimize sexual aggression (Acceptance of Modern Myths About Sexual Aggression [AMMSA] scale) among heterosexual men at postintervention and at 3-month follow-up.

The secondary objectives are

To evaluate the effects of the REVISE intervention on empathy, gender role attitudes, relationship functioning, and communication patterns.To assess changes in physiological responses (eye tracking and pupillometry) during the IVR experience across experimental conditions.To explore participants’ subjective experiences and perceived changes following the intervention through qualitative interviews, and to integrate these findings with quantitative outcomes.

It is hypothesized that participants exposed to identity-swapping with sexual harassment scenarios will show greater reductions in beliefs legitimizing sexual aggression compared to the control conditions.

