#### Pupillometry

It is the measurement of minute fluctuations in pupil diameter in response to a stimulus. Pupil dilation is thought to index autonomic activity; thus, negative stimuli trigger larger pupil dilation [49,50]. Pupillometry has recently been used to effectively evaluate the emotional effect of a nonconsented sex film clip visualization (woman as recipient) in men [50]. We will compute the pupil diameter ratio. Pupil data will be sampled at least 60 Hz, with a visual angle accuracy of 0.5. Pupil amplitude artifacts (<1 mm or >9 mm) as well as drifts and blinks will be coded as missing values [51]. As suggested, pupil data will be smoothed using a 10 Hz low-pass filter as suggested by Carvalho et al [52].

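### The pupillometry model is fixed as random intercepts only, with the number of values per man left open; if several rows per man per period enter it, the test of within-session change across arms is anti-conservative

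*Protocol article*

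**What the plan says.** All places are in the Methods of the protocol article.

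- **Objectives.** The second secondary objective is "To assess changes in physiological responses (eye tracking and pupillometry) during the IVR experience across experimental conditions".
- **Data Analysis Plan, Secondary Outcomes.** Physiological responses are among the outcomes given "prespecified mixed-effects models with the same fixed-effects structure as the primary model", that is, condition, time and their interaction. For eye tracking and pupillometry the section then says that the measures "will be analyzed using linear mixed-effects models with random intercepts for participant and, where applicable, for stimulus item". It names no random slope, no participant-by-period effect and no residual correlation.
- **Couple-Level Dependence.** "This clustering is addressed through the inclusion of couple-level random effects in all mixed-effects models". GEE with an exchangeable working correlation is added as a sensitivity analysis.
- **Pupillometry.** "Pupil data will be sampled at least 60 Hz"; "pupil data will be smoothed using a 10 Hz low-pass filter"; "We will compute the pupil diameter ratio". The number of ratios per man or per phase is not given.
- **Intervention Procedure.** In phase 3 "men will have a 180-second adaptation period", followed by the scene, during which pupils are recorded in all three conditions. The length of the scene is not given.

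**The concern.** Table 1 schedules physiological measures on the intervention day only. For the pupil, the time factor borrowed from the primary model can therefore only mean periods within the session, and the contrast that answers the objective is condition by period.

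A random intercept removes a man's general level. It does not allow men to differ in how much their pupil changes from one period to the next, nor does it allow neighbouring readings to be correlated. If several rows per man per period enter the model, the standard error of the change contrast is driven by the number of rows, when it should be driven by the number of men.

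The article counts physiological indicators among the strengths of its multimodal design and promises 95% confidence intervals for all outcomes. A chance arm difference in pupil change could then look like objective support for the self-report results.

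**Working it through.** **The plan's own figure.** There is none for pupillometry; the sample size of 84 couples (90 recruited) concerns the primary outcome. The only design figures used here are three arms of 30 men and the 180-second adaptation period (180 × 60 = 10,800 samples per man at 60 Hz).

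**Assumptions, because the documents give no values.** Two periods of 180 s; within-man SD of the signal set to 1; serial correlation that decays exponentially with a correlation time of 1 s; SD between men of the true change, ω, from 0 to 0.5 of the within-man SD.

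**Formula.** Let m be the number of averaged bins per period, L = 180/m the bin length in seconds, and v the variance of a bin mean, v = 2/L − (2/L²)(1 − e^(−L)). Correlation between neighbouring bins is ignored.

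- True variance of one man's change: D = ω² + 2v/m.
- Residual mean square of the random-intercept model: s² = [(2m − 2)v + (m/2)D] / (2m − 1).
- Variance of the change that the model assumes: M = 2s²/m.
- Variance ratio: R = D/M.
- With three arms the interaction test has 2 numerator degrees of freedom. With many denominator degrees of freedom its type I error is about 0.05^(1/R).

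**Two checks on the formula.** With m = 1, s² = D/2, so M = D, R = 1 and the error is 5%. One value per man in each of two phases is therefore valid whatever ω is. With ω = 0, s² = v, so again R = 1. For averaged bins the inflation comes from men differing in their change.

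**Worked case, m = 3, ω = 0.5.** L = 60, v = 0.0328. D = 0.25 + 0.0219 = 0.2719. s² = (4 × 0.0328 + 1.5 × 0.2719)/5 = 0.1078. M = 2 × 0.1078/3 = 0.0719. R = 3.78. Error = 0.05^(1/3.78) = 0.45.

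**Worked case, m = 18, ω = 0.5.** L = 10, v = 0.18. D = 0.27. s² = (34 × 0.18 + 9 × 0.27)/35 = 0.2443. M = 0.0271. R = 9.95. Error = 0.74.

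**Simulation under no arm effect**, 30 men per arm, three arms, 800 runs per cell, with the formula in brackets:

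| ω | 1 value per phase | 3 bins | 6 bins | 18 bins |
|---|---|---|---|---|
| 0 | 4.6% (5.0%) | 4.4% (5.0%) | 5.4% (5.0%) | 5.8% (5.0%) |
| 0.1 | 3.5% (5.0%) | 11.9% (10.6%) | 13.6% (11.9%) | 13.4% (13.2%) |
| 0.3 | 4.8% (5.0%) | 35.0% (34.4%) | 46.0% (45.1%) | 56.6% (54.1%) |
| 0.5 | 3.0% (5.0%) | 43.9% (45.3%) | 61.4% (61.4%) | 75.2% (74.0%) |

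**Denser rows (simulation only).** With rows 1 s apart, serial correlation alone (ω = 0) gives 21% to 30%, and ω = 0.5 gives 87% to 89%. Raw 60 Hz rows give 88% to 99% with correlation times of 0.2 to 1 s. They stay at 4% to 4.5% only if samples were independent and ω = 0.

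**Average level.** The main effect of condition was rejected in 3% to 7% of runs in every setting, because the participant intercept already carries a man's overall level.

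**The case against.** The strongest objection is that the article never makes samples, seconds or bins the rows of the model. The 60 Hz figure is a recording rate, and the Pupillometry section announces a derived ratio. A reader might infer that the raw 60 Hz stream is modelled and that false positives are therefore far above 5%. The documents do not support that inference, and the 88% to 99% figures must not be read as the error rate of this plan. With one value per man in each of two phases the model is valid. This objection stands and makes the point conditional.

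The ratio may also already be relative to the adaptation period, in which case the arm comparison is one of average level and holds near 5%. Its definition and number per man may be in the full protocol or analysis plan, so their absence from the article is not held against it. This stands too. However, if that ratio is a single value per man, the participant intercept in the stated model cannot be separated from the residual, so the model sentence still does not fit.

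It would be wrong to say that only a participant intercept is used, since stimulus-item and couple intercepts are also named. In an analysis of men alone the couple intercept coincides with the man's own and does not help.

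Finally, the GEE sensitivity analysis could expose the problem. A sandwich test clustered on the man rejected in 5.3% to 6.4% of simulated runs, and a small direct GEE fit in 9.5% (200 runs, one setting). The article does not say that robust errors will be used, and a sensitivity analysis does not repair the main model.

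**Conclusion.** The point holds in conditional form. The article commits to a random-intercepts-only model for an outcome whose objective is within-session change, without tying that model to a unit of analysis. The model suits one reading (one value per man in each of two phases). It is over-specified for a single ratio per man and anti-conservative for condition by period when a period contributes several rows per man.

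In that last case the type I error was about 12% to 75% with 3 to 18 bins per phase, and higher with denser rows. These sizes rest on assumed between-man SDs of change (0.1 to 0.5 of the within-man SD), a 1 s correlation time and 180 s periods. If all men share the same change, binned data show no inflation. Tests of average level between arms are not at risk.

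This is a minor point on one secondary outcome. The primary AMMSA analysis is unaffected.

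**What to change.** In the Secondary Outcomes paragraph of the analysis plan, replace the pupil part of the model sentence. State that each man contributes one summary, his mean pupil diameter over the scene divided by his own mean over the 180-second adaptation period, and that the three arms are compared on it by linear regression with one row per man. That analysis is valid on every reading of the present text.

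If several values per period are to be modelled, add a participant-by-period random effect or an unstructured covariance, and do not rely on random intercepts alone.

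The cost is a sentence or two, before recruitment begins. The downside is that the time course of the pupil response becomes a descriptive plot.
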